## Abstract

**Background:**

University students in Indonesia are exposed to stressors such as high academic task load, financial strains, and relationship problems. Therefore, they are at risk of developing symptoms of common mental disorders, such as depression and anxiety (i.e., psychological distress). However, there is a gap between the number of mental health professionals and the number of students in need of a psychological intervention. Self-Help Plus (SH+), a guided group-based stress management intervention developed by the WHO, was adapted to the population and context to address barriers in accessing mental health care among students in Indonesia. The aim of the APRESIASI study is to assess the effectiveness and cost-effectiveness of SH + in reducing psychological distress among university students in Indonesia.

**Methods:**

The SH + intervention will be tested in a pragmatic superior randomized controlled trial (RCT) with two parallel arms. SH + will be tested among Indonesian university students with symptoms of psychological distress (Patient Health Questionnaire-9; PHQ-9 ≥ 5.5 < 20). The participants (*n* = 296) will be randomized into either the intervention group that receives SH + with enhanced care as usual (ECAU), or into the ECAU only with a 1:1 allocation ratio. The primary outcome is the reduction in psychological distress assessed with the Patient Health Questionnaire Anxiety and Depression Scale (PHQ-ADS) at three-month follow-up. The secondary outcomes are symptoms of depression, anxiety, perceived stress, functioning, resilience, quality of life, identified problems, treatment acceptability, and cost-effectiveness.

**Discussion:**

To our knowledge, SH + is the first a transdiagnostic, face-to-face, and group-based intervention to be tested for its effectiveness in reducing psychological distress in Indonesia. If shown to be effective, SH + has the potential to be scaled up across university settings.

**Trial registration:**

ISRCTN15761598, 14/07/2023.

**Supplementary Information:**

The online version contains supplementary material available at 10.1186/s40359-025-03026-y.

## Background

Emerging adulthood reflects the period during which individuals aged 18 to 29 transitions from adolescence into adulthood. During this developmental period, they are faced with living away from their parents, pursuing education, entering the workforce, and finding a partner [1]. However, this period is also marked by a high prevalence of common mental disorders such as depression and anxiety [2, 3]. A study of emerging adults in Indonesia reported a 28.86% prevalence of depression [4] and most emerging adults in a qualitative study reported feeling anxious, with half of the respondents reporting self-harm and having suicidal thoughts [5].

The period of emerging adulthood coincides with the period of going to university. Compared with the general population, psychological distress appears to be more common and severe among university students [6]. The WHO Mental Health Survey International College students project revealed that more than 30% of students at 19 universities in eight countries screened positive for at least one common mental health disorder [7]. In the context of Indonesia, previous studies have indicated that university students exhibit symptoms of psychological distress [8], with high level of stress ranging from 37 to 50% [9, 10], a prevalence of depression between 18.8% and 25% [10, 11], and an anxiety prevalence of 51% [10]. Another study found that Indonesian university students had an increased risk of self-harm and suicide attempt [12].

Given the high prevalence of mental health problems among university students, there is a growing concern in universities to address the mental health problems of their students. Therefore, the establishment of counselling centres for students is part of a government initiative called SIMKATMAWA (System of Performance Information and Student Governance) [13]. While these centres may provide important support and reflect the growing awareness of mental health issues in higher education, there are currently no factual data on how many universities in Indonesia have mental health facilities, the qualifications of the mental health professionals involved, or the number of students utilizing these services. Furthermore, as an alternative, students can visit mental health professionals outside universities. However, there is a large gap between the number of people who need mental health interventions and the availability of such services, known as the mental health gap [14]. In the university context, there is a gap between the number of undergraduates, which exceeds eight million [15], and the availability of clinical psychologists, which is only 4000 [16]. Therefore, the implementation of low-intensity [17] and transdiagnostic interventions is proposed to meet the needs of emerging adults with common and multiple mental health problems [18, 19].

The World Health Organization (WHO) developed a range of scalable low-intensity psychological interventions that are based on transdiagnostic and task-sharing principles. One of these interventions is Self Help Plus (SH+), which is a group-based (up to 30 people) stress management course for adults, delivered by a non-specialist. It was developed based on acceptance commitment therapy (ACT) [20]. SH + consists of a pre-recorded program delivered in a group setting over five two-hour sessions, supplemented by a self-help book named *Doing What Matters in Times of Stress: An illustrated Guide* [21].

SH + has been adapted and implemented in humanitarian settings in Uganda [22], Turkey [23], refugees resettling in European countries [24], and workers in nursing facilities [25]. Furthermore, based on three RCTs in those sites, SH + was found to be effective in reducing psychological distress in adults and preventing the onset of mental disorders (e.g., depression), as were improvements in general health functioning, and subjective well-being [22, 24, 25] and in reducing economic and societal costs related to disability [26].

In the present study, we have adapted SH + to the Indonesian language and culture. We will conduct a randomized controlled trial (RCT) to compare the effectiveness of SH + combined with enhanced care as usual (ECAU) to ECAU only in reducing psychological distress in university students in Indonesia.

## Goals and hypotheses

The primary objective of the study is to evaluate the effectiveness and cost-effectiveness of a culturally adapted SH + intervention combined with ECAU among university students in Indonesia at a three-month follow-up (main time point) in reducing psychological distress. The secondary objectives are to assess depression and anxiety symptoms separately, as well as perceived stress, functioning, quality of life, resilience, identified problems, feasibility, and acceptability. In addition, moderator variables influencing the reduction in psychological distress, anxiety, and depression symptoms and improvements in functioning and quality of life will be explored.

Previous research on SH + among South Sudanese female refugees in Uganda found that SH + reduced psychological distress three months after the intervention [22]. In addition, a follow-up period of three months is long enough to observe the sustained effects of the intervention while minimizing loss to follow-up and recall bias. In the context of our university student population, a three-month timeframe also aligns with academic terms, thereby reducing the risk of attrition due to changes in academic circumstances or different types of activities. For example, some students may have to enrol in an internship programme or live in a rural community for a full semester. Therefore, we expect that SH + with ECAU (SH+/ECAU) will be superior to the ECAU only in reducing psychological distress (primary outcome) at three-month follow-up, as well as the secondary outcomes of depression and anxiety, perceived stress, improved functioning, quality of life, resilience, and identified problems. Furthermore, we expect that SH+/ ECAU will report lower healthcare costs than ECAU-only.

## Method

### Research design

This is a pragmatic, single-blind RCT with two parallel arms. This RCT will be conducted following the Consolidated Standard of Reporting Trials (CONSORT) [27] (see Fig. 1).

**Fig. 1 Fig1:**
[figure not shown]
Flowchart of the randomized controlled trial according to CONSORT

### Study setting

The Adapted Self-Help Plus (SH+) to Reduce Psychological Distress among University Students In Indonesia (APRESIASI) project is led by Vrije Universiteit Amsterdam (VU) in collaboration with Universitas Padjadjaran (Unpad), Indonesia. Participants will be recruited from two universities, namely Unpad and Institut Teknologi Bandung (ITB), located near the city of Bandung, West Java.

### Participants

#### Inclusion criteria

University students aged between 17 and 29 years old.Score ≥ 5.5 [28] on the Patient Health Questionnaire-9 (PHQ-9) [29].Willingness to attend five sessions of SH+.

#### Exclusion criteria

Acute medical conditions requiring immediate hospitalization;score ≥ 20 (severe depression symptoms) on PHQ-9 based on Kroenke et al. (2001);indication of imminent risk of suicide or self-harm or other life-threatening risk based on Suicide Ideation Scale (SIS) [30] with score ≥ 21.89 [31];evidence of severe cognitive impairment related to mental, neurological or substance abuse based on the PM + observation checklist [32];started, stopped or significantly changed pharmacotherapy in the previous eight weeks;specialized psychological treatment (e.g., cognitive behavioural therapy, psychoanalysis) initiated or discontinued in the past eight weeks.

### Procedure

#### Recruitment

Several strategies will be used to recruit participants for this study. As a first strategy to identify participants, an online mental health survey will be conducted among university students. Advertisements about mental health surveys will be posted on universities’ and students’ social media. This advertisement will contain information about the mental health survey and the link for participating in the survey. In the survey link, the students will read the information about the study and are asked to provide consent before they fill out the survey form. Participants with psychological distress (PHQ-9 ≥ 5.5), who are eligible according to the above-mentioned inclusion and exclusion criteria and who give permission to be followed-up after completion of the survey, will be contacted for further interviews. During this interview, the RCT will be explained, and they will be asked whether they are interested in participating in the RCT.

As a second strategy, advertisements about the RCT will be distributed through all social media at the universities, faculties, work units and student organisations. This advertisement will include a short explanation of the study, the contact details of the research assistant and a form to take part in the study. If anyone has questions about the study or needs further information about participation, they can contact the research assistant via e-mail or WhatsApp. In addition, the university counselling centre will be asked to actively promote RCT to students through their regular activities.

If a student expresses interest in participating in the study, they will fill in the registration form, which consists of their name, email address, contact details, and confirmation of their availability to attend the scheduled SH + sessions. The research assistant then sends the information letter of the project, the digital personal informed consent link, and privacy statement to their email. They will have one week to read the information and decide whether to participate. The research assistant will send out a reminder on the 6th and 10th days after the information letter has been sent out.

SH + is a group-based intervention, so each participating university will need to enrol at least 40–60 participants. The SH + session will start after one and a half months of recruitment. We will continue to keep the recruitment process open until the required number of participants has been reached.

#### Screening

Screening (t_0_) will be carried out via a Zoom video call (20–30 min) with a trained research assistant and consists of a self-report questionnaire (sociodemographic information and PHQ-9). If the result of PHQ-9 ≥ 5.5 but < 20, the participant will be screened for exclusion criteria by asking specific questions (e.g., “are you currently receiving psychological counselling or psychotherapy?”) and by an observation checklist completed by the research assistant (e.g., “does the participant understand you?”). Screening will stop if the participant meets any of the exclusion criteria.

#### Assessment

Data will be collected through self-report assessments at four times points: *t*_*1*_ (baseline – sent at least 10 days before the SH + to the participants already enrolled), *t*_*2*_ (post-SH+, week-7), *t*_*3*_ (main time point – 3 months after SH+), and *t*_*4*_ (follow-up – 6 months after SH+) with the Castor Electronic Data Capture (EDC) software program [33]. Each assessment will be provided via e-mail with a link to the self-report questionnaire to each participant and can be completed on any device with internet access. The time to complete each assessment is approximately 20–30 min. If an assessment remains incomplete, the participant will receive a maximum of three reminders on days 3, 7, and 10 through various communication channels to encourage retention. The participants will receive IDR 50,000 e-money for each completed assessment, with a maximum of four e-money awards (*t*_*1*_ to *t*_*4*_).

#### Assessors

The screening process is carried out by a trained research assistant with at least a bachelor’s degree in psychology who currently receives training to become a psychologist. During a video call, the research assistant will explain the study once again. The research assistant will be blinded to the group allocation.

#### Randomization

The participants will be randomly assigned to either the intervention or the control group at a 1:1 allocation ratio, using randomization with four and six blocks. The randomization will be performed by CASTOR EDC. Due to the nature of the study, the participant will know their group allocation, either it is an SH+/ ECAU or ECAU only. The research coordinator will know the results of the randomization.

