#### Facilitators

SH + will be delivered by two facilitators (a pair), and each university will have two to four facilitators. SH + facilitators have at least a bachelor’s degree in psychology. Individuals with a bachelor’s degree in psychology and who are currently in training to become a psychologist can be a facilitator.

There will be open recruitment to become a facilitator, and recruitment will start during the preparation of the study and before the recruitment of the study participants. The facilitator will receive up to 40 h of training based on the SH + training manual [54], and the total number of hours will depend on the skills and experience of the facilitators already has. The training will be conducted by the coordinator of this study (DA) or a clinical psychologist who has been trained by the coordinator of this study. The training will consist of basic helping skills, SH + facilitating skills, and managing participants’ distress, explaining the aims and background of the SH + intervention.

In addition to delivering SH+, the facilitator will be the one to contact participants to inform them of their randomization allocation. The facilitator will deliver the ECAU (i.e., leaflet) to all participants via email or media communication of the participant’s choice.

The clinical supervisor and facilitator will receive remote support and supervision from the research coordinator as needed. The facilitator will have an online group meeting with the supervisor who is a clinical psychologist to discuss protocol adherence, review barriers or potential barriers, facilitator concerns, any adverse effects and serious adverse events.

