### Analysis

#### Sample size

By utilizing G*Power [55], considering psychological distress as the primary outcome with an effect size of 0.3, a power calculation for a repeated measures design suggests a minimum sample size of *N* = 148 (power = 0.95, α = 0.05, rho = 0.9) to detect the expected effect size. Accounting for a 50% attrition rate observed during our pilot, a total of 296 participants will be recruited (148 participants in each arm). At each university, there is an intervention group and a control group. Each group will consist of 20–30 participants.

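### The stated group structure holds 80–120 participants, not 296; the number of SH+ groups should be stated, and allocation should be blocked within university

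*Protocol article*

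**What the plan says.** Four places in the protocol article bear on this.

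- **Study setting:** "Participants will be recruited from two universities".
- **Sample size:** a minimum of 148 is doubled for 50% attrition to 296, given as 148 in each arm. The same paragraph ends: "At each university, there is an intervention group and a control group. Each group will consist of 20–30 participants".
- **Recruitment:** because the intervention is delivered in groups, "each participating university will need to enrol at least 40–60 participants". The same section adds: "We will continue to keep the recruitment process open until the required number of participants has been reached".
- **Randomization:** participants are "randomly assigned to either the intervention or the control group at a 1:1 allocation ratio, using randomization with four and six blocks", carried out in Castor EDC. No stratification factor is named.

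Two further sections matter. Facilitators work in pairs and "each university will have two to four facilitators". The mixed model under Data analysis lists time as a fixed effect, baseline PHQ-ADS as a covariate and participant as a random effect; university is not listed.

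**The concern.** The Sample size paragraph gives a total and a structure that do not fit together. A reader who needs to know how many SH+ groups will run, how many rounds there are and how many people sit in each cannot get this from the article, and the one structure it describes is too small for the target by a wide margin.

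This bears on allocation as well. SH+ is delivered face to face, so each group has to be formed from students of one university who were allocated to SH+ in the same period. Permuted blocks balance the arms within whatever list they are drawn for. If that list covers both universities, balance holds overall but not within each university, and the size of each SH+ group is left partly to chance. The arms may then also differ in their mix of students from the two universities, and the model as listed has no term to absorb that.

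**Working it through.** **1. The plan's own total.** Inputs: minimum 148 and attrition 50% (Sample size). 148 / (1 − 0.5) = 296, or 148 per arm. The figure reproduces. The minimum of 148 is taken as given here.

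**2. What the stated structure holds.** Inputs: two universities (Study setting), one intervention and one control group at each, 20–30 per group (Sample size).

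- Lower end: 2 × 2 × 20 = 80
- Upper end: 2 × 2 × 30 = 120
- Gap to target: 296 − 120 = 176, up to 296 − 80 = 216

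Per university this is 40–60, the same range that Recruitment gives as a minimum. So that range describes a single round with one group per arm. An even split of the full sample would be 296 / 2 = 148 per university.

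**3. Groups needed for 148 in the SH+ arm.**

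- Fewest: 148 / 30 = 4.9, so five groups (average 29.6)
- Most: 148 / 20 = 7.4, so seven groups (average 21.1); eight would average 18.5, below the stated range

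The compatible range is five to seven. With an even split, each university has 74 in the SH+ arm. Three groups average 24.7 and fit; two would average 37 and four would average 18.5. An even split therefore means three groups at each university, six in all. Five or seven arise with an uneven split, for example three groups at one university and four at the other. Two to four facilitators per university is one or two pairs, so three groups at a university take two or three rounds.

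**4. Balance within a university.** Assumptions: equal numbers enrolled at the two universities, arriving in random order; blocks of 4 and 6 mixed at random. D is the difference between the arms within one university that enrols U.

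| U | Shared list: median of D | Shared list: 95th percentile of D | Blocks by university: maximum D |
|---|---|---|---|
| 40 | 4 | 8 | 2 |
| 50 | 4 | 10 | 2 |
| 60 | 4 | 10 to 12 | 2 |

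At U = 60 the percentile lies on a boundary: the hypergeometric probability of a difference of 12 or more is 0.044, so a simulation may return 10 or 12. The maximum of 2 applies to even U; an odd U cut off halfway through a block of six can give 3.

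**5. Chance that either arm at a university falls outside 20–30.**

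| U | Shared list | Blocks by university |
|---|---|---|
| 40 | about 0.82 | about 0.23 |
| 50 | about 0.03 | 0 |
| 60 | about 0.85 | about 0.22 |

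The high values at 40 and 60 arise because an exact split is then the only result inside the range. Counting the SH+ group alone on a shared list, the chance of fewer than 20 at U = 40 is 0.41 and the chance of more than 30 at U = 60 is 0.43.

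**The case against.** **The trial is not planned to stop at 80–120.** This stands. The Recruitment figure is a minimum, recruitment stays open until the required number is reached, 296 is stated outright, and two facilitator pairs could run groups side by side. A reader might infer from the stated structure that the trial will be far too small and lose most of its power. The documents do not support that; they point to repeated or parallel groups. What remains is that no section says so, and the sentence on groups contradicts the total given just before it.

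**The article does not say the list is unstratified.** This also stands. A reader might take the description as one list shared by both universities. The Randomization section gives only the ratio, the block sizes and the software, and an article may leave strata to the full protocol or the Castor set-up. Likewise, the model description is a summary that does not spell out even the treatment term, so the absence of university there is not proof that it will be left out. These two items can be raised as improvements to confirm, not as errors.

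**The breaches of 20–30 are concentrated at the ends of the range.** Correct. Near 50 per university and round they are rare even on a shared list, and at 40 or 60 blocking by university still leaves about 22–23%. No section attaches a consequence to a group of 19 or 31. In the control arm, which receives an e-leaflet, group size plays no part in delivery.

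**Conclusion.** The inconsistency in the Sample size section is established by arithmetic on the protocol's own figures: a target of 296 against a stated structure that holds 80–120. Five to seven SH+ groups reconcile the two, taking 20–30 to mean participants allocated to a group rather than those who attend. This is a defect of description. It does not show that the trial will under-recruit.

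The allocation part is conditional. If the Castor blocks are not generated by university, doing so reduces the 95th percentile of the arm difference within a university of 40–60 from roughly 8–12 to at most 2, assuming equal university sizes. The group-size range is then also better kept, though not guaranteed, and this matters mainly when enrolment per round is near 40 or 60. If the list is already stratified, only the wording needs attention. A model term for university is sensible in either case, because it would match the way groups are formed and would absorb differences between the two student populations. No figure is available for the precision gained.

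**What to change.** 1. **Sample size section:** replace the sentence on one group per arm per university with the planned number of SH+ groups. Five to seven in total are compatible with 148 in the SH+ arm at 20–30 per group: three at each university if recruitment is even, with up to four at one university if it is not. Say whether they run in successive or parallel rounds, and align the Recruitment minimum by describing it as per round.
2. **Randomization section:** state whether the Castor blocks are generated separately by university. If not, set this up before the first inclusion, keeping the varying block sizes. Aiming for about 50 per university and round, rather than 40 or 60, would also help keep groups within range.
3. **Data analysis section:** add university as a fixed effect in the primary and secondary models.

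The cost is a few sentences, one software setting and one model term, with no extra participants. The Trial status section reports that, as of December 2024, the trial had not started and the first inclusion was expected in March 2025. Item 2 is simple only before that point; items 1 and 3 can still be made later, provided the model is fixed before the data are analysed.
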